#### 2.8.7. Objective PA Levels

Patient energy expenditure (kcal), steps per day, sedentary behavior (minutes/wk) and light, moderate, and vigorous intensity PA (minutes/wk) [49] will be measured at pre- and 12 weeks post-intervention via accelerometers (ActiGraph wGT3X-BT, ActiGraph Corp., Pensacola, FL, USA) [62]. [name] and an RA will instruct patients to wear the accelerometer using an elastic strap with placement aligned on the hip/anterior iliac crest of their nondominant hand side except when swimming, bathing, showering, or sleeping. The ActiLife6 full version software (version 6.0, ActiGraph Corp., Pensacola, FL, USA) [63] will be used to initialize and download accelerometer data. [name] will verify complete accelerometer data, defined as having ≥60% of wear time during waking hours on four consecutive days including two weekends and two weekdays. Waking hours will be calculated based on the reported sleep hours on the TLFB-E. If patients have incomplete data, they will be asked to re-wear the accelerometer for a second attempt.

### 2.9. Other Outcome Measures

#### 2.9.1. Fidelity of P3-EX and PAVS Implementation

Each time physicians use P3-EX and PAVS with their patients, we will assess the degree to which these ExRx methods are implemented as intended by obtaining the usage time (minutes) to prescribe the FITT ExRx to each patient. For P3-EX, we will also obtain the frequency of each selected ACSM strategy used to prioritize the CVD risk factor chosen by the physician when there are multiple CVD risk factors tied for the greatest risk.

#### 2.9.2. Physician and Patient Trial Satisfaction

Physicians and patients will complete open-ended written questions, administered by [name], to obtain qualitative feedback [64] on their satisfaction with the pilot trial and inform the design of a larger trial. Within 48 h after completing the delivery of both P3-EX and PAVS, physicians will provide their thoughts on the recruitment procedures and the brief ExRx training they received. Patients will provide their thoughts on use of the TLFB-E and virtual exercise guidance study visits after they complete the intervention. [name] will work with RAs to independently and manually code responses and identify common themes for each question, and resolve any discrepancies with [name] and [name]

#### 2.9.3. Harms

Patients will be asked to report any adverse events they experience during the trial to [name], who will document internal or external adverse events using the Institutional Review Board (IRB) Event Accumulation Tracking Log. [name] will notify [name], [name], and [name], who will be blinded to group assignments. [name], [name], and [name] will grade the severity of patient adverse events according to their respective institution criteria, assess the need for disclosure to the physician, and report any serious events to the IRB within 7 calendar days. All other adverse events will be submitted at the time of continuing the IRB review.

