#### 2.6.3. 12-Week Exercise Intervention

[name], an ACSM-certified exercise professional, with assistance from RAs, will provide patients with virtual weekly oversight of their unsupervised ExRx for 12 weeks, performed at a location the patients prefer. During the first week, [name] will email all patients to provide a 12-week ExRx information packet (Supplementary File S3) containing standardized and progressive FITT exercise recommendations for the ExRx they received [25], and patients will attend a one-on-one virtual study visit led by [name] over Microsoft Teams to receive standardized exercise guidance. [name] will use a script to walk patients through exercise definitions and examples and how to monitor exercise intensity and progress the FITT of exercise. Throughout the intervention, [name] will email all patients weekly to provide their ExRx FITT exercise goals for the upcoming week. Patients will use a validated exercise diary called the *Timeline Followback for Exercise* (TLFB-E) [49] to record the FITT of exercise they perform daily for the 12-week exercise intervention. [name], with assistance from RAs, will monitor the TLFB-E for each patient to assess their adherence to the intervention and challenges they may be having. [name] will email all patients with weekly feedback by providing their TLFB-E summary report from the previous week. After completing 6 weeks of the intervention, patients will attend a second one-on-one virtual study visit led by [name], using a script, to inform patients how they are faring following their ExRx by reviewing their TLFB-Es and strategies to improve exercise adherence.

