### 2.11. Data Collection Methods

Physicians and patients will record all survey responses and exercise diary recordings electronically in Research Electronic Data Capture (REDCap) forms, a secure web application contracted by the primary hospital institution responsible for the trial. [name] will assess all vitals, body composition, and objective and subjective PA level outcomes using standardized operating procedures and record all measurements in REDCap case report forms. [name] will follow standardized laboratory measurement protocols to assess each outcome [59,65,66], and provide patients with privacy during in-person study visits to complete their survey responses. RAs, trained by [name], will assist [name] with the assessment of exercise adherence and coding of open-ended survey questions. [name], with assistance from RAs, will pilot test all instruments and REDCap surveys and forms before the start of the trial.

[name] will send reminder emails to physicians and patients for scheduled study visits, and up to three reminder emails to encourage rescheduling or survey completion if there is noncompliance. We will discontinue data collection from physicians and patients who withdraw from the study but will retain any data obtained from them. We will continue data collection for patients regardless of their adherence to the intervention. [name] will record any known reasons for withdrawal from the trial, noncompliance with study procedures, or non-adherence to the exercise intervention.

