### 4.3. Limitations

We acknowledge potential limitations with the P3-EX Feasibility Trial. Physicians may experience burden of recruiting two of their patients to participate in the study. However, given that preventive care is one of the most common reasons for office-based physician visits [81], we anticipate that a high proportion of patients will be eligible. Concerning blinding, other than laboratory technicians assessing blood lipid-lipoproteins and glucose, we will not include other blinded outcome assessors. [name] will have knowledge of patient group assignments when conducting patient exercise guidance virtual visits and assessing vitals, body composition, and objective and subjective PA levels at post-intervention. [name] will therefore follow standardized laboratory operating procedures [59,65,66] to minimize observer bias, which include following outcome measurement protocols, providing privacy to patients during in-person survey completions, and reading standardized exercise guidance scripts. Although the TLFB-E is potentially susceptible to social desirability bias, we will cross reference the TLFB-E with the accelerometer at pre- and post-intervention. Last, concerning the study design, the trial does not include a non-exercise control group, which may hinder the ability to interpret the efficacy of P3-EX for improving patient PA levels or CVD risk factors. Nonetheless, this pilot data will inform the efficacy of P3-EX compared to generic ExRx approaches in routine medical care.

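### Section 2.9.3 states only patient report as the route for adverse events, with no fixed harms question in the diary or scripted visits, so events that do not stop exercise are likely to be under-captured

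*Protocol article*

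**What the plan says.** The Harms section (2.9.3) describes how events are collected and processed.

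- **Collection:** "Patients will be asked to report any adverse events they experience during the trial to" a study-team member, "who will document internal or external adverse events using the Institutional Review Board (IRB) Event Accumulation Tracking Log".
- **Notification and grading:** that person notifies three others, "who will be blinded to group assignments". Three people, apparently the same ones, "will grade the severity of patient adverse events according to their respective institution criteria", and serious events go to the IRB within 7 calendar days.

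The scheduled patient contacts are described elsewhere.

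- **Diary (2.6.3, 2.8.6):** patients use the TLFB-E "to record the FITT of exercise they perform daily for the 12-week exercise intervention". Section 2.8.6 lists its content as frequency, type, time and intensity. Staff monitor it for adherence and for challenges, and a summary goes back to the patient each week.
- **Visits (2.6.3):** a scripted virtual visit in week 1 gives exercise guidance. A second, after six weeks, reviews the diaries and ways to improve adherence.
- **Platform (2.11):** "Physicians and patients will record all survey responses and exercise diary recordings electronically", in REDCap.
- **Blinding (4.3):** the person giving the guidance "will have knowledge of patient group assignments when conducting patient exercise guidance virtual visits".

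Section 4.2 says that goal setting, feedback and self-monitoring are used in both arms.

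**The concern.** A request to report events leaves the patient to decide what counts and when to mention it. Events that stop exercise tend to surface anyway, through missed sessions or withdrawal. A strain, a dizzy spell or an unplanned medical visit after which the patient carries on need not. The patients are inactive adults with cardiovascular risk factors who exercise unsupervised for 12 weeks.

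Three things are at stake.

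- **Safety review:** Section 2.15 plans no stopping guidelines. The team's safety response is prompted by multiple adverse events or dropouts suspected of being linked to a procedure or intervention. That prompt works only on events that have been captured.
- **What the pilot can say about harms:** a low count under patient report alone could reflect few events or few reports, and the data could not separate the two.
- **Balance between arms:** a P3-EX patient receives a personalised prescription with special exercise considerations (2.6.1), a PAVS patient a general handout (2.6.2). What patients are told to look out for could affect what they mention.

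**Working it through.** **1. The stated contacts side by side**

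| Contact | Stated content | Harms question stated? |
|---|---|---|
| Daily TLFB-E diary (2.6.3, 2.8.6) | Frequency, intensity, time and type of exercise | No |
| Weekly email (2.6.3) | Goals for the coming week, summary of the past week | No |
| Week-1 virtual visit, scripted (2.6.3) | Exercise definitions, intensity monitoring, progression | No |
| Virtual visit after week 6, scripted (2.6.3) | Diary review, adherence strategies | No |
| Post-intervention assessment (2.8) | Risk factors, accelerometry, questionnaires | No |
| Patient report (2.9.3) | Any adverse event | Patients are asked to report; no form, interval or wording given |

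**2. What the other safeguards reach**

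- Diary review for challenges (2.6.3) is not a fixed question, and the listed diary fields hold exercise data only.
- Section 2.11 records known reasons for withdrawal, noncompliance and non-adherence. That reaches events that change behaviour, not events after which the patient continues as before.
- Grading (2.9.3) acts on events already reported and logged.

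**3. Illustration of size**

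The article gives no adverse-event rate and no reporting rate, so there is no figure of its own to reproduce. The one input from the document is 24 patients per group (2.13). The true per-patient risk *p* and the share *s* of affected patients whose event is reported are assumptions.

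Expected number of affected patients recorded in an arm = 24 × *p* × *s*. 
Chance of recording none in an arm = (1 − *p* × *s*)^24.

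| *p* (assumed) | *s* (assumed) | Expected recorded | Chance of none |
|---|---|---|---|
| 10% | 100% | 24 × 0.10 = 2.4 | 0.90^24 = 8% |
| 10% | 50% | 24 × 0.05 = 1.2 | 0.95^24 = 29% |
| 10% | 30% | 24 × 0.03 = 0.72 | 0.97^24 = 48% |
| 20% | 100% | 24 × 0.20 = 4.8 | 0.80^24 = 0.5% |
| 20% | 50% | 24 × 0.10 = 2.4 | 0.90^24 = 8% |
| 20% | 30% | 24 × 0.06 = 1.44 | 0.94^24 = 23% |

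At a lower risk of 5%, the chance of recording at least one affected patient in an arm is 1 − 0.95^24 = 71% with full capture and 1 − 0.975^24 = 46% with half. Over all 48 patients it is 1 − 0.95^48 = 91% and 1 − 0.975^48 = 70%.

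**4. Uneven reporting**

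If the true risk is equal in both arms, the apparent risk ratio is *s*₁/*s*₂. Reporting of 70% against 50% gives 0.70/0.50 = 1.4. Reporting of 70% against 30% gives 0.70/0.30 = 2.33. Equal reporting leaves it at 1.0. Nothing in the document shows which case applies.

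**The case against.** The strongest reply is that this is a condensed article. The visit scripts, the patient information packet, the REDCap forms, the patient schedule figure and the full protocol are not at hand, and any of them might contain a harms question. Asking patients to report also fits a question put at each contact. This tempers the point without removing it. The article does more than stay silent: it has a Harms section with a stated collection method, and it lists the content of the diary and visits in detail without a harms item.

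Several stronger readings are tempting, and the documents do not support them.

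- **That events will be under-counted.** This is a likely consequence, not a demonstrated one. Diary review and recorded reasons for non-adherence will bring some events to light.
- **That events are reported to the unblinded person who gives the exercise guidance.** Names are removed from the text. It says only that those notified are blinded, and does not say so of the recipient.
- **That capture will differ by arm.** Route, diary and visit schedule are the same in both arms. Different prescription content makes a difference possible, no more.
- **That the trial loses a planned safety comparison or harm rates for the next trial.** Comparative safety is in neither aim (1.2). The Conclusions speak of using secondary-outcome data to power a later efficacy trial, and harms are listed under other outcome measures. With 24 per arm, even complete capture would support little comparative inference.

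The blinded notification and apparent blinded grading are real strengths and should be credited.

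**Conclusion.** The concern holds in a limited form. The only stated route for adverse events is patient report to one team member who is not described as blinded. The existing electronic diary and scripted visits, common to both arms, are not said to ask about harms. Events that do not stop exercise are therefore likely to be under-captured, and uneven capture cannot be excluded.

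The size is unknown. Across the assumed 10% to 20% risk and 30% to 50% capture, the chance of recording no affected patient in an arm runs from 8% to 48%, against 0.5% to 8% with full capture. These figures rest wholly on the assumed rates and on patients being independent. The conclusion also assumes that the unseen forms and scripts add no harms question; if they do, the article need only say so. The primary usability analysis is unaffected. This is worth changing before the first patient starts, because weeks in which nobody asked cannot be recovered reliably.

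**What to change.** In section 2.9.3, add a fixed item to the weekly REDCap TLFB-E form, worded identically in both arms: any new injury, symptom or medical visit this week, yes or no, and if yes the onset date and whether exercise was missed. Read the same item from the script at the virtual visit after week 6 and ask it again at the post-intervention visit. Keep volunteered reports as an additional source, and keep the blinded grading as it is.

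The cost is one item on an existing form and a line at each of two existing visits. The downside is slight patient burden and more minor events to log and grade. No treatment or clinical rule changes.

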### 2.10. Physician and Patient Trial Timeline

Schematic diagrams outlining the physician and patient schedule of enrollment, intervention delivery, and outcome assessments that were previously described are outlined in Figure 3 and Figure 4, respectively [36].

### 2.11. Data Collection Methods

Physicians and patients will record all survey responses and exercise diary recordings electronically in Research Electronic Data Capture (REDCap) forms, a secure web application contracted by the primary hospital institution responsible for the trial. [name] will assess all vitals, body composition, and objective and subjective PA level outcomes using standardized operating procedures and record all measurements in REDCap case report forms. [name] will follow standardized laboratory measurement protocols to assess each outcome [59,65,66], and provide patients with privacy during in-person study visits to complete their survey responses. RAs, trained by [name], will assist [name] with the assessment of exercise adherence and coding of open-ended survey questions. [name], with assistance from RAs, will pilot test all instruments and REDCap surveys and forms before the start of the trial.

[name] will send reminder emails to physicians and patients for scheduled study visits, and up to three reminder emails to encourage rescheduling or survey completion if there is noncompliance. We will discontinue data collection from physicians and patients who withdraw from the study but will retain any data obtained from them. We will continue data collection for patients regardless of their adherence to the intervention. [name] will record any known reasons for withdrawal from the trial, noncompliance with study procedures, or non-adherence to the exercise intervention.

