### 2.13. Sample Size Estimation

We conducted a power analysis using G*Power (version 3.1.9.6, Heinrich Heine University Düsseldorf, Düsseldorf, Germany) [68] to obtain a conservative usability rating of P3-EX to evaluate the primary aim of the study. We obtained the lowest observable usability score of 4.650 ± 0.759 (mean ± SD) converted from our feasibility survey study pilot data [32] to compare to the null hypothesis middle score of 4.0 on the mHealth Application Usability Questionnaire [50]. Using a one-sided Wilcoxon signed-rank (one sample case) test [69] at the significance level (α) of 0.01 and calculated effect size between the observed and middle score of Cohen’s d = 0.856, we determined that 19 physicians are required to achieve 85% power. Therefore, we will use 19 physicians to achieve 85% power (α of 0.01), and recruit two patients per physician to complete 38 patients. Using an observed attrition of 20% for patients in the study [70,71,72,73], this trial will aim to recruit 24 physicians and 48 patients (24 patients per group). Because physicians’ PA levels could influence how they perceive and rate the delivery of an ExRx [45], we aim to recruit half of the physicians who meet PA guidelines (n = 12) [44] and half who do not (n = 12).

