### 2.15. Trial Management and Monitoring

[name] will work with an independent data safety monitoring committee within the university institution to oversee data collection, analysis, and interpretation plans ([name], [name], [name], [name], and [name]), to ensure the integrity of trial data related to P3-EX. Committee members will meet virtually with [name], when appropriate, to discuss and validate protocol and procedural conduct related to data collection, and methods for statistical analysis and interpretation. There are no planned interim analyses or stopping guidelines for this trial.

[name], with oversight from [name], will keep records of physician and patient recruitment, enrollment, compliance with study procedures, attrition, and study completion throughout the trial, and report de-identified progress updates or issues to [name] during weekly virtual meetings. If there are multiple adverse events or dropouts that are suspected of being associated with a specific study procedure or intervention, [name], [name], [name], [name], and [name] will discuss and devise a course of action if deemed necessary. [name] and [name] will provide weekly virtual administrative oversight of RAs to ensure conduct and compliance with the study protocols.

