#### 2.16.1. Consent Process

[name], who will obtain consent from physicians and patients, has completed informed consent training required by the institutions and read all procedures. [name] will obtain electronic informed consent in REDCap from physicians during the virtual orientation visit, and from patients during their first study visit. [name] will provide a verbal study overview, and physicians and patients will read through the form and ask any questions before they decide to participate and e-sign. Physicians and patients will be informed that any data collected in the trial might be used in future studies and they may voluntarily withdraw from the study at any time without penalty or loss of benefits. Physicians and patients will receive a PDF copy of the informed consent for their records.

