#### 2.16.3. Ancillary Care and Post-Trial Care

Patients will be compensated USD 50 after they complete 6 weeks of exercise intervention, and another USD 50 after they complete the study. Physicians will not receive compensation. Patients will receive healthcare during their healthcare appointment with their physician, and this trial is relatively low risk, therefore ancillary care during the trial or post-trial care will not be provided. The hospital institutions will not provide compensation for trial-related harm.

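### Section 2.11 ends all data collection when a patient withdraws, with no exception for adverse events, which fits poorly with the plan's own harms and dropout review

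*Protocol article*

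**What the plan says.** Section 2.11 (Data Collection Methods) sets the rule at withdrawal: "We will discontinue data collection from physicians and patients who withdraw from the study but will retain any data obtained from them". The next sentence treats non-adherence differently: "We will continue data collection for patients regardless of their adherence to the intervention". The same paragraph adds that a member of the study team "will record any known reasons for withdrawal from the trial, noncompliance with study procedures, or non-adherence to the exercise intervention".

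Section 2.9.3 (Harms) relies on self-report: "Patients will be asked to report any adverse events they experience during the trial to" a member of the study team. Events are then graded for severity, and serious ones go to the IRB within 7 calendar days. Section 2.15 (Trial Management and Monitoring) makes dropouts a possible safety signal: "If there are multiple adverse events or dropouts that are suspected of being associated with a specific study procedure or intervention", the investigators are to discuss a course of action. Section 2.16.1 (Consent Process) tells participants that "they may voluntarily withdraw from the study at any time without penalty or loss of benefits".

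Section 2.13 (Sample Size Estimation) gives the planning figure for loss: "Using an observed attrition of 20% for patients in the study".

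**The concern.** The rule at withdrawal covers every kind of data. Nothing in the article separates efficacy and questionnaire data, where stopping is natural, from adverse events, where the participant's safety and the trial's harms record are both involved.

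Two provisions elsewhere depend on information that this rule cuts off. Grading and serious-event reporting need the course of an event, not only its first report. The dropout review needs to know whether harm played a part in leaving and what happened next, yet only reasons that happen to be known are recorded and no one is told to ask. In a pilot with 24 patients per group that is meant to inform a larger trial, even one or two events with an unknown outcome would weaken what can be said about harms.

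**Working it through.** The point rests mainly on setting the sections side by side. Arithmetic gives only a scale.

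**1. What each section needs and what the withdrawal rule leaves**

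| Situation | What happens under the article |
|---|---|
| Patient stops exercising but stays in the study | Collection continues (2.11) |
| Event reported before withdrawal | Kept (2.11) |
| Harm as the reason for withdrawal | Recorded if known (2.11); no duty to ask |
| Event open at withdrawal, outcome unknown | Not collected (2.11); grade stays as last reported (2.9.3) |
| Event that becomes serious after withdrawal | Not collected (2.11), so it may never reach the serious-event reporting in 2.9.3 |
| New event after withdrawal | Not collected (2.11) |

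The first three rows are wholly or partly covered. The last three are not. The regular contacts that could prompt a report are the weekly emails, the diary review and the visit after week 6 (2.6.3). The article states no other route once a patient has left.

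**2. Reproducing the planning figure**

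Inputs from 2.13: 19 physicians and 38 patients to complete, 20% attrition.

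- Physicians: 19 / (1 − 0.20) = 23.75, rounded up to 24.
- Patients: 38 / (1 − 0.20) = 47.5, rounded up to 48.

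Both agree with the article. The planned patient loss is 48 − 38 = 10 (0.20 × 48 = 9.6).

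**3. Scale of follow-up affected**

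The article does not say how many of these losses would be withdrawals from the study, or when they would occur. As an upper illustration, assume that all 10 withdraw at the same week *w* of the 12-week intervention. Total planned follow-up is 48 × 12 = 576 patient-weeks, and the part without harm collection is 10 × (12 − *w*).

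| Assumed week of withdrawal | Patient-weeks without harm collection | Share of 576 |
|---|---|---|
| 0 | 120 | 20.8% |
| 3 | 90 | 15.6% |
| 6 | 60 | 10.4% |
| 9 | 30 | 5.2% |

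These are shares of follow-up time, not of events. Turning them into a missed event rate would need event rates before and after withdrawal, and the article gives none. No sample size, power or alpha figure depends on this point.

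**The case against.** The strongest reply has three parts.

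First, ending collection when someone chooses to leave a study is ordinary, and withdrawal here is voluntary. That stands as far as it goes. It does not rule out asking for permission to follow an open event, and a patient who refuses would be left alone.

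Second, the harm that prompts a withdrawal comes before it. Patients are asked to report events throughout, weekly oversight looks for difficulties, reports already made are kept and known reasons are recorded. This also stands, and it limits the point to what is unresolved, unasked or new at the time of leaving.

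Third, a journal article condenses the full protocol, which may hold the safety follow-up rules. This would answer a complaint about missing detail. Here, however, the article states a rule without qualification. If the full protocol does allow such follow-up, the article's sentence conflicts with it and needs aligning.

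A reader might also take section 2.16.3, which says that "ancillary care during the trial or post-trial care will not be provided", to mean that open events have no recorded outcome. That section is about providing care, not about collecting data, and does not support the inference.

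**Conclusion.** The point holds as a modest, inexpensive correction. As written, section 2.11 leaves events that are open, worsen or become serious after withdrawal uncaptured and requires no question about harm at exit, so it needs reconciling with 2.9.3 and 2.15.

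Its reach is about 10 of 48 patients, on the assumption that all planned attrition is withdrawal from the study. The real number may be smaller or larger.

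Several stronger readings are tempting but not supported:

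- That those who withdraw are the patients most likely to have left because of harm. The documents say nothing about why patients would leave.
- That recorded harm rates would be understated by a particular factor, such as a half. This needs assumed event counts and the further assumption that none of the withdrawers' events is captured, contrary to the retention of earlier reports.
- That the loss would favour the more demanding prescription. The article describes one personalised and one generic prescription and does not rank them by demand.
- That a physician's withdrawal ends follow-up of that physician's patients. Section 2.11 does not say so.

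**What to change.** Amend the withdrawal sentence in section 2.11 along these lines: when a patient withdraws, study procedures and efficacy data collection stop. Unless the patient declines further contact, the study team asks whether any adverse event has occurred or contributed to the decision to leave, and records the outcome of any event open at that time.

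Add a matching line to 2.9.3, so that grading and serious-event reporting extend to such events, and to 2.15, so that the dropout review uses the exit answers. Make sure the consent form covers this contact and the right to refuse it.

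The cost is a few sentences of protocol and consent text, IRB notification of the change, and a short contact or two for about 10 patients on the planned attrition. Some will decline, so capture will improve without being complete. The design, sample size and primary analysis are unaffected.
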